### Adverse events committee

This committee consists of 3 independent physicians (medical oncologist, radiation oncologist and surgeon) and decides on the final diagnostic classification of critical clinical events. For all serious adverse events the documentation and relevant patient data are verified by the co-ordinating personnel before submitting the data to the Adverse Events Committee for diagnostic classification.

Analysis of safety related data is performed with respect to frequency of:

• Serious Adverse Events and Adverse Events stratified by body-system

• Adverse Events stratified by severity

• Adverse Events stratified by causality.

Patient toxicities will be assessed using the NCI Common Toxicity Criteria (CTC). Toxicity will be evaluated pretreatment, weekly during chemoradiation/ chemotherapy, prior to each course of infusional 5-FU and at follow-up. Unacceptable toxicity is defined as unpredictable, or irreversible Grade 4 toxicity. Decisions regarding weekly chemoradiation treatment and chemotherapy dose-adjustment will be made using the guidelines below and based on hematological parameters (ANC and platelets) monitored weekly during chemoradiation before each dose of cisplatin.

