### Study objectives

The primary objective is to compare the overall survival at two years postoperatively between two different methods of adjuvant treatment: therapy with 5-FU, cisplatin, interferon alpha 2b combined with radiation and the standard treatment from the ESPAC-1-Trial with 5-FU plus folinic acid.

Secondary objectives are to determine the role and the mechanism of interferon alpha 2b in patient's chemoradiation regimen, the toxicity, the disease-free interval and the quality of life. Different factors are tested in terms of their potential role as predictive markers.

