In study arm A the patients receive post-chemoradiation 5-FU infusions of 200/mg/m^2 ^/day by continuous intravenous infusion on days 64–101 and 120–161. The timing of these courses of infusional 5-FU will be adjusted in patients who have treatment interruptions.

Patients in study arm B will be treated with 20 mg/m^2 ^intravenous bolus injection of Folinic acid, D-L form, followed by 425 mg/m^2^/day intravenous bolus injection of 5-FU given on 5 consecutive days every 28 days for 6 cycles, i.e. 24 weeks.

The treatment protocol is outlined in figure 1.

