### Investigation schedule and follow-up

Pre-treatment evaluation for patients who are enrolled in study arm A includes a single low-dose (3 Mio U) injection of INTRON A prior to therapy (LDI). Blood will be drawn for intensive immunological studies. All patients (study arm A or B) must have appropriate lab and radiographic studies (CXR; CT abdomen [done post-operatively]; CBC; platelet count; BUN; creatinine; bilirubin, CA 19-9, and CEA) conducted prior to study enrolment to meet eligibility criteria.

During days 1–38 [study arm A] or during chemotherapy [study arm B] patients will be assessed with laboratory evaluation: complete blood count and blood chemistries weekly. Laboratory parameters in study arm A will be evaluated before each dose of cisplatin. Creatinine will be determined also one day after administration of cisplatin. Blood from members of study arm A will be investigated weekly for immunological markers.

Vital signs (blood pressure and pulse rate) and temperature are controlled daily during treatment. Patients are evaluated prior to receiving chemoradiation or chemotherapy. Patients enrolled in study arm A are evaluated weekly by the medical oncology and radiation oncology team during treatment. The team will check patients at each visit for symptoms due to therapy; a physical examination and complete safety labs should be performed. The patients' mental state will be investigated weekly. The questionnaire CES-D will be used as support. The three module questionnaire will be filled out during weeks 3 and 6 (study arm A) or week 3 and week 24 for study arm B.

During post-chemoradiation, infusional 5-FU (Study Arm A) patients will be evaluated by a physician prior to treatment and every 2 to 3 weeks with clinical assessment and laboratory parameters including a CBC, electrolytes, BUN, and creatinine. If patients undergo post chemoradiotherapy infusional 5-FU coordinated by an outside medical oncologist, a study nurse will contact the patient at least once weekly by telephone.

In the post-treatment period patients will be seen every 3 months by the surgical service for the first 2 years, every 4 months for the third year, and every 6 months during the 4th and 5th post-treatment years.

The aggregate clinical, laboratory, and imaging evaluations required per protocol as well as the timing of the optional three module questionnaire are outlined in table 1.

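### After day 38 arm A is assessed for toxicity less often than arm B, so short-lived toxicity in arm A may be under-recorded; the net direction of any distortion over the whole treatment is not established

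*Protocol article*

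**What the plan says.** The Study objectives section of the protocol article lists "the toxicity, the disease-free interval and the quality of life" among the secondary objectives. The Adverse events committee section plans to analyse adverse events as frequencies, including by severity, graded with the NCI CTC.

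Treatment lasts about equally long in both arms (Randomisation and standardised treatment scheme). Arm B's chemotherapy is "given on 5 consecutive days every 28 days for 6 cycles, i.e. 24 weeks". Arm A has chemoradiation on days 1–38 and then 5-FU "by continuous intravenous infusion on days 64–101 and 120–161".

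The assessment schedule appears in two places:

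- **Investigation schedule and follow-up.** Blood counts and chemistries are weekly in both arms at first, but the window differs: "During days 1–38 [study arm A] or during chemotherapy [study arm B] patients will be assessed with laboratory evaluation". For arm B that means all 24 weeks. In arm A's later 5-FU courses, "patients will be evaluated by a physician prior to treatment and every 2 to 3 weeks with clinical assessment and laboratory parameters". If an outside oncologist coordinates those courses, "a study nurse will contact the patient at least once weekly by telephone".
- **Adverse events committee.** "Toxicity will be evaluated pretreatment, weekly during chemoradiation/ chemotherapy, prior to each course of infusional 5-FU and at follow-up". For infusional 5-FU this names only the pre-course grading and the follow-up visits.

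The Investigation schedule section also gives arm A, and only arm A, a weekly evaluation by the medical and radiation oncology team during treatment, and a creatinine test on the day after each cisplatin dose. Vital signs are taken daily during treatment with no restriction to one arm.

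**The concern.** The recorded frequency of an adverse event, and the worst grade seen, depend on how often the patient is examined. A transient fall in blood counts or a short biochemical abnormality is found by weekly sampling and can fall between visits two or three weeks apart. If one arm is sampled weekly and the other every two to three weeks over the same calendar period, a comparison of frequencies by severity reflects the visit schedule as well as the treatment.

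This matters here because the Statistical considerations section sets no stopping rule on overall toxicity; it treats even frequent reversible toxicity as acceptable if the survival gain is large. Weighing benefit against toxicity then relies on the reported toxicity comparison, and brief reversible toxicity is the kind that sparse sampling misses.

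The text also leaves open when toxicity is graded in arm A after day 38: every 2 to 3 weeks in one section, only before each course and at follow-up in the other. The sentence on weekly team evaluation during treatment sits with the chemoradiation text, but read literally it conflicts with both.

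**Working it through.** **Inputs from the protocol article.** Arm B: 6 cycles of 28 days, weekly laboratory work. Arm A: days 1–38 weekly; days 64–101 and 120–161 before treatment and every 2 to 3 weeks.

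**Input assumed.** Length of a toxicity episode. The document gives none, so 7 to 21 days is shown.

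**1. The plan's own figure.** 6 × 28 / 7 = 24 weeks, as stated for arm B.

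**2. Arm A durations.** Chemoradiation 38 days; second course 101 − 64 + 1 = 38 days; third course 161 − 120 + 1 = 42 days. Later courses together: 38 + 42 = 80 days. On treatment in total: 38 + 80 = 118 days.

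**3. Planned looks.** Each later course is counted from a check on its first day.

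| Window | Arm B | Arm A, every 2 weeks | Arm A, every 3 weeks |
|---|---|---|---|
| Days 1–38 | 6 | 6 (days 1, 8, 15, 22, 29, 36) | 6 |
| Days 64–101 | 6 | 3 (days 64, 78, 92) | 2 (days 64, 85) |
| Days 120–161 | 6 | 3 (days 120, 134, 148) | 2 (days 120, 141) |
| Whole treatment | 24 | 12 | 10 |

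The arm B total also includes its weekly looks outside these windows. On the literal reading of the Adverse events committee section, arm A has 2 gradings between day 39 and follow-up, against 24 − 6 = 18 in arm B.

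**4. Chance that an episode is seen.** For an episode of D days and visits S days apart, with detection only at visits, capture = min(1, D/S).

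| D | S = 7 | S = 14 | S = 21 |
|---|---|---|---|
| 7 days | 1.00 | 0.50 | 0.33 |
| 10 days | 1.00 | 0.71 | 0.48 |
| 14 days | 1.00 | 1.00 | 0.67 |
| 21 days | 1.00 | 1.00 | 1.00 |

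**5. Arm A relative to arm B over arm A's 118 treatment days.** Equal true rates per treatment day are assumed. Arm B's capture is 1.00 for every D in the table, so the ratio is (38 × 1 + 80 × min(1, D/S)) / 118.

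- D = 7: (38 + 40) / 118 = 0.66 at S = 14; (38 + 26.7) / 118 = 0.55 at S = 21.
- D = 10: (38 + 57.1) / 118 = 0.81; (38 + 38.1) / 118 = 0.64.
- D = 14: 118 / 118 = 1.00; (38 + 53.3) / 118 = 0.77.
- D = 21: 1.00 at both spacings.

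The whole shortfall comes from the 80 later days. In days 1–38 the laboratory schedules match.

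**The case against.** A reader might infer that the toxicity comparison as a whole is biased in favour of the experimental arm. The document does not support that. In days 1–38, when arm A receives cisplatin, interferon and radiation, laboratory sampling is weekly in both arms, and arm A has the team evaluation and the extra creatinine test on top. Those checks may raise its recorded toxicity by an amount the document does not allow one to estimate. Serious events, deaths and lasting toxicity depend little on visit spacing, and treatment-related deaths are monitored throughout.

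Three further inferences also fail or are insecure:

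- The weekly telephone contact does not replace the 2- to 3-weekly evaluation. It is an addition in arm A when an outside oncologist coordinates.
- The prose gives no separate schedule for days 39–63 and 102–119, but the investigation schedule is in Table 1, which is not available, so no gap can be claimed.
- The laboratory list for the later courses is introduced as examples, so it need not be shorter than arm B's.

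For arm B, the Investigation schedule section states only the laboratory work as weekly; weekly toxicity grading there rests on the Adverse events committee section.

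It is also fair to say that the choice of assessments entering a toxicity table is commonly left to the analysis plan. That stands as far as the tables go. It does not cover the visit schedule, which the article itself fixes differently by arm, or the disagreement between its two sections. Distortions running in opposite directions in different phases do not cancel reliably; they make a pooled comparison harder to read.

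**Conclusion.** The point holds in a limited form. After day 38 planned assessment is less frequent in arm A than in arm B, at about 24 against 10 to 12 looks over the whole treatment, and short-lived toxicity in arm A's later 5-FU courses may be under-recorded. The relative capture is about 0.55–0.66 for 7-day episodes, 0.77–1.00 for 14-day episodes and 1.00 for 21-day episodes.

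These ratios rest on assumed episode lengths, equal true rates, detection only at scheduled visits and courses given on the stated days. Detection between visits, including through the telephone contact, would bring them closer to 1. If toxicity is graded in that phase only before each course and at follow-up, the shortfall is larger. The net direction over the whole treatment is not established. The primary survival comparison is not affected.

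**What to change.** Leave each arm's safety monitoring unchanged, and:

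1. Reconcile the Adverse events committee section with the Investigation schedule section on when toxicity is graded in arm A after day 38, including what the weekly team evaluation covers.
2. Record CTC grades on the same form in both arms at every contact already planned, including the 2- to 3-weekly evaluations and the weekly telephone contact.
3. Report all toxicity by arm, but base the between-arm comparison on phases: days 1–38, where laboratory sampling is weekly in both arms, separately from the later period.
4. Give the number of assessments per patient by arm and phase, and add a supplementary analysis of the later period limited to comparable assessment times.

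A fixed 3-weekly grid counted from treatment start would fit badly. Day 105, for example, falls between arm A's courses (days 102–119), those courses move after interruptions, and the grid would meet arm B's 28-day cycles at changing cycle days. Comparing by phase avoids this and discards no data.

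The cost is protocol and form wording, slightly more form completion and analysis, and a whole-treatment toxicity comparison that is less simple to present.

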## Background

Only 10–20% of patients with pancreatic cancer can be resected with curative intent at the time of diagnosis. Loco-regional recurrence and/or metastatic disease develop in the majority of patients who undergo pancreatic resection. Relapse occurs within 9–15 months after initial presentation and patients have median life expectancies of only 12–15 months without adjuvant therapy. The 5-year survival rate of patients with resected pancreatic adenocarinoma is approximately 20% [1]. The statistics for the 80 to 90 % of patients who present with locally advanced and metastatic pancreatic cancer are even more dismal. Rarely do such patients achieve a complete response to treatment; median survival is 5–10 months and 5-year survival is near zero [2].

There is very little randomised data on adjuvant therapy for pancreatic carcinoma. The ESPAC-1 trial assessed the role of adjuvant therapy in a randomized study. 548 patients were enrolled in Europe in this first large randomized trial. There was evidence that adjuvant chemotherapy brought survival benefits. The five-year survival rate was 21 percent among patients who received chemotherapy [3].

In 1995 a phase II trial was initiated by the Virginia Mason Clinic, Seattle, USA combining pancreaticoduodenectomy and adjuvant therapy with 5-FU, cisplatin, interferon alpha and radiation therapy. Picozzi et al. reported treatment and results in a series of 43 patients with high-risk resected pancreatic adenocarcinoma (84% node positive, 19% margin positive). After a median follow-up period of 32 months the 2-year survival rate was 64% and the 5-year survival rate was 55% [4]. The overall recurrence rate was 12% of which 80% occurred within 2 years after surgery [5].

Since the Virginia Mason group reported such encouraging results in improving survival periods, there has been considerable interest in gaining increased experience with this therapy combination in an effort to confirm results and evaluate the toxicity profile of a modified version of this regimen.

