### Randomisation and standardised treatment scheme

A block-randomisation-list is generated via computer system (SAS Version 8.2, SAS Institute Inc., Cary, USA). The sealed randomisation list is stored in the investigator file. Patients are randomised using sealed opaque envelopes in the independent study centre at the Department of Surgery (Clinical Study Centre – "Klinisches Studienzentrum Chirurgie" – KSC) until informed consent is attained and diagnostic procedures rule out any contra-indication for participation in this trial.

After randomisation and pre-treatment evaluation treatment must begin within 12 weeks of surgery. A port catheter will be placed after informed consent and randomisation will be done within one to two weeks after pancreatoduodenectomy for patients in study arm A. These patients will be treated with 200 mg/m^2^/day 5-FU by continuous intravenous infusion at days 1–38.

Cisplatin – 30 mg/m^2 ^(maximum single cisplatin dose of 60 mg) iv over 60 minutes on days 1, 8, 15, 22, 29, 36 (6 doses). Two to three hours before and after cisplatin administration the patients will receive hydration of at least 2 litres.

Interferon alpha-2b (Intron A) will be administered at a dose of 3 million units subcutaneously three times weekly (Monday, Wednesday, and Friday) for 17 doses. Non-steroidal anti-inflammatory drugs and steroids should be avoided if possible during Intron A treatment.

External beam radiation is to be given concurrently with chemotherapy with a total dose of 50.4 Gy in 28 fractions over 5.5 weeks (1.8 Gy/day). The pancreatic bed (i. e. resection margin) will be covered with a minimum margin of 2 cm. The hepatoduodenal ligament, origins of the celiac axis and superior mesenteric artery will be included. The AP/PA fields must include the entire duodenal C-loop as seen on the pre-operative CT scan. All patients will receive XRT per informed consent. A four-field technique with AP/PA and lateral fields and customised blocking is required. The beams will be weighted more heavily in the AP/PA fields (usually 2:1 compared to the lateral fields). The dose contribution from the lateral fields should be restricted to 20 Gy. Simulation should be done with the patient in the supine position with "arms up" position. A dosage greater than or equal to 10 MV photons should be used.

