### Statistical considerations and sample size estimation

The primary endpoint in this study is the overall survival period, measured from the date of resection. The sample size calculation is based on the assumption of a constant monthly hazard rate of 0.044 in the standard group and a constant monthly hazard rate of 0.021 in the experimental group. The hazard values are derived from two-year survival rates in the study groups (using the formula λ_group _= -1 × ln(P_24,group_)/24) with a two-year survival rate of 35% in the control group [11,12]and a conservative two-year survival rate of 60% in study arm A[13].

Assuming an accrual period of 18 months and a follow-up of 42 months [14,15], testing for a difference in hazard (hazard ratio ≠ 1) on level α = 0.05 and with a power of 80% a study sample size of 96 patients is needed. Taking into consideration the estimate of approximately 14 patients which will not complete the treatment, a total number of 110 patients should be randomised.

The overall survival will be summarised by Kaplan-Meier estimate and differences in therapy protocols will be analysed by univariate Cox-regression.

Various secondary endpoints will be evaluated in this study as well. Disease free survival, measured from date of operation, will be summarised by Kaplan-Meier estimate.

One year after inclusion of the first patient an interim analysis will be carried out which could result in stopping arm B. The planning of the study is based on a fix sample approach and not on groups sequential. Because the alpha level of the interim analysis is set to α = 0.001, the sample size calculated from a group sequential approach will be similar to the sample size of the fixed study approach.

The main evaluation will be performed two years after the last patient's enrolment.

There will be explicit stopping rules in place to terminate the trial early in the unlikely event that an unacceptably high rate of treatment related deaths (TRD) is observed. TRD will be monitored using the design of Thall and Simon [16]. A non-informative Beta prior distribution (i.e., B (0.015, 0.085) for TRD rate is assumed. The trial will be stopped if at any point during the trial there is a greater than 90% probability that the true TRD rate is greater than 0.05. Each patient will subsequently be evaluated and, an independent safety board will be consulted in making decision.

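### Follow-up visits are counted from the end of treatment but disease-free survival from the operation, so relapse dating can differ by arm if delays or early stopping differ

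*Protocol article*

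**What the plan says.** *Investigation schedule and follow-up* sets the visits: "In the post-treatment period patients will be seen every 3 months by the surgical service for the first 2 years". The later visits keep the same anchor: "every 6 months during the 4th and 5th post-treatment years". The section refers the imaging evaluations to Table 1, which is not part of the text at hand.

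*Statistical considerations and sample size estimation* uses a different origin: "Disease free survival, measured from date of operation, will be summarised by Kaplan-Meier estimate". The primary endpoint has the same surgical origin: "The primary endpoint in this study is the overall survival period, measured from the date of resection".

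*Randomisation and standardised treatment scheme* determines how far apart the two clocks can be. The start is bounded on one side only: "treatment must begin within 12 weeks of surgery". Arm A ends with 5-FU "by continuous intravenous infusion on days 64–101 and 120–161", and "The timing of these courses of infusional 5-FU will be adjusted in patients who have treatment interruptions". Arm B has six 28-day cycles, given as 24 weeks.

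On the timing of relapse, *Background* says: "Relapse occurs within 9–15 months after initial presentation".

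**The concern.** A relapse without symptoms is recorded when someone looks for it. If the looking follows the end of treatment, the recorded disease-free interval depends partly on when treatment began, was interrupted or stopped, as well as on the disease. Two patients with the same true relapse date can then have different recorded dates.

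A shift common to both arms only blurs the curves. A shift that differs between arms biases the comparison. The regimens here are quite different: chemoradiation with three drugs followed by infusions, against bolus chemotherapy. It is therefore plausible that interruptions and early stopping will not be balanced. The disease-free interval is a named secondary objective of an open trial, and later analysis cannot fully recover relapse dates that were never observed at comparable times.

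**Working it through.** **Inputs.** From the article: start of treatment no later than week 12 after surgery (no earliest start is given, so week 0 is only a lower bound); arm A chemoradiation ends on day 38 and arm A treatment on day 161; arm B has six 28-day cycles with injections on 5 days each; visits every 3 months after treatment; about 14 of 110 patients not completing. Assumed: 3 months = 91 days, 30.44 days per month, equal allocation (55 per arm).

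**The plan's own figure.** Arm B: 6 × 28 = 168 days = 24 weeks, as stated. Counted to the last injection, arm B ends on day 5 × 28 + 5 = 145. The text does not say which of the two opens the post-treatment period, so both are carried.

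**Planned difference between arms (B minus A).** (145 − 161)/30.44 = −0.5 months, or (168 − 161)/30.44 = +0.2 months.

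**First post-treatment visit, months after surgery** = (start delay + last treatment day + 91)/30.44.

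| Start after surgery | Arm A, day 161 | Arm B, day 145 | Arm B, day 168 | Arm A stopped at day 38 |
|---|---|---|---|---|
| week 0 | 8.3 | 7.8 | 8.5 | – |
| week 4 | 9.2 | 8.7 | 9.4 | 5.2 |
| week 8 | 10.1 | 9.6 | 10.3 | 6.1 |
| week 12 | 11.0 | 10.5 | 11.3 | 7.0 |

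For example, arm A from week 4: (28 + 161 + 91)/30.44 = 9.2. Completers in both arms are thus first seen after treatment at about 8 to 11 months.

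**What moves an individual's calendar.**
- Start delay: up to 84/30.44 = 2.8 months, under the same rule in both arms.
- Interruption in arm A: each week of postponement moves all later visits by 7/30.44 = 0.23 months.
- Stopping arm A at day 38, if follow-up then begins: (161 − 38)/30.44 = 4.0 months earlier than an arm A completer and (168 − 38)/30.44 = 4.3 months earlier than an arm B patient completing 24 weeks.

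**Range for the difference between arms.** Suppose all 14 expected non-completers stop at day 38 (an assumption).
- Split evenly, 7/55 = 12.7% per arm: the mean first visit moves earlier by 0.127 × 123 = 15.7 days in arm A and 0.127 × 130 = 16.5 days in arm B. The difference is under 1 day.
- All in arm A, 14/55 = 25.5%: arm A moves by 0.2545 × 123 = 31.3 days, about 1.0 month, and arm B not at all.

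These are shifts in the mean first visit, not in disease-free survival. Once the 3-monthly visits are running, a relapse waits on average half an interval, 1.5 months, whatever the anchor. The effect therefore falls mainly on relapses before the first post-treatment visit. If relapse times were exponential with a median of 9 to 15 months (an assumption loosely suggested by *Background*), 34% to 50% would have relapsed by month 9 and 40% to 57% by month 11.

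**The case against.** The strongest reply is that the planned calendars are nearly the same: half a month or less apart against a 3-month interval. Disease-free survival is secondary, the article says only that it will be summarised by Kaplan-Meier, and overall survival does not depend on visit timing. All of this stands and limits the consequence.

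A reader might infer that relapse is first looked for at 9 to 11 months, when it is already under way. The documents do not support this. Table 1 may list imaging during treatment. The text also describes clinical contact on treatment: weekly team evaluation in arm A, then a physician every 2 to 3 weeks; weekly laboratory tests and evaluation before chemotherapy in arm B. The 9 to 15 months in *Background* run from presentation, not surgery, and are a rough benchmark only.

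A reader might also infer a large spurious contrast. Take a start at day 60, relapse medians of 9 to 15 months, and 25% of arm A stopping at day 38. Those stoppers are seen at (60 + 38 + 91)/30.44 = 6.2 months, by when 25% to 38% would have relapsed, so observed 9-month disease-free survival is 91% to 94% in arm A against 100% in arm B. This rests on three things that the documents do not give:
- Relapse is found only at visits.
- Virtually all expected non-completers are in arm A and stop on the same day.
- Deaths are ignored. If deaths count as events, which the article does not spell out, the article's control hazard alone gives 9-month survival of exp(−0.044 × 9) = 67%, so 100% could not be observed.

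Nor does follow-up necessarily open at day 38. The article allows further chemotherapy after withdrawal, so such a patient need not yet be in a post-treatment period.

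None of this removes the mismatch of origins, which the text states outright.

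**Conclusion.** The point holds as a modest design weakness confined to disease-free survival. Visits follow the end of treatment, the endpoint follows the operation, and the gap between them varies with start delay, interruptions and early stopping. For completers the planned arms differ by −0.5 to +0.2 months, and the first post-treatment visit comes about 8 to 11 months after surgery in both.

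Bias between arms is conditional on delays or early stopping differing by arm. Using the article's own 14 non-completers, and assuming equal allocation and stopping at day 38, early stopping shifts the difference between arms in mean first visit by anything from practically nothing (even split) to about 1 month (all in arm A). Which applies is unknown. The resulting error in disease-free survival is smaller to the extent that relapse is found through symptoms, on-treatment contact or imaging in Table 1. The article does not show that the comparison is biased, only that its schedule does not protect against such bias.

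**What to change.** In *Investigation schedule and follow-up* and in Table 1, schedule the relapse assessments every 3 months for the first 2 years from one common date. The operation is the natural choice because it is the origin of disease-free survival; randomisation would also serve. The times should be the same in both arms and should hold whether treatment is completed, delayed or stopped. Where an assessment coincides with an existing treatment visit, the two can be combined. If Table 1 already does this, keep the schedule and make the text agree with it.

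The cost is a change of wording in the protocol and possibly in Table 1. The 3-month interval stays. One or two assessments fall within the treatment period, and visits are no longer evenly spaced from the last dose.
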